# Does telecare prolong community living in dementia? A study protocol for a pragmatic, randomised controlled trial

**DOI:** 10.1186/1745-6215-14-349

**Published:** 2013-10-23

**Keywords:** Assistive technology, Telecare, Dementia, Randomised control trial, Independence, Community living

## Abstract

**Background:**

Assistive technology and telecare (ATT) are relatively new ways of delivering care and support to people with social care needs. It is claimed that ATT reduces the need for community care, prevents unnecessary hospital admission, and delays or prevents admission into residential or nursing care. The current economic situation in England has renewed interest in ATT instead of community care packages. However, at present, the evidence base to support claims about the impact and effectiveness of ATT is limited, despite its potential to mitigate the high financial cost of caring for people with dementia and the social and psychological cost to unpaid carers.

**Method/design:**

ATTILA (Assistive Technology and Telecare to maintain Independent Living At Home for People with Dementia) is a pragmatic, multi-centre, randomised controlled trial over 104 weeks that compares outcomes for people with dementia who receive ATT and those who receive equivalent community services but not ATT. The study hypothesis is that fewer people in the ATT group will go into institutional care over the 4-year period for which the study is funded. The study aims to recruit 500 participants, living in community settings, with dementia or significant cognitive impairment, who have recently been referred to social services.

Primary outcome measures are time in days from randomisation to institutionalisation and cost effectiveness. Secondary outcomes are caregiver burden, health-related quality of life in carers, number and severity of serious adverse events, and data on acceptability, applicability and reliability of ATT intervention packages. Assessments will be undertaken in weeks 0 (baseline), 12, 24, 52 and 104 or until institutionalisation or withdrawal of the participant from the trial.

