### Assessments

Assessments will be undertaken by local investigators employed by the ATTILA team in weeks 0 (baseline), 12, 24, 52 and 104. All local investigators are researchers with clinical experience.

Following an assessment of mental capacity (and therefore ability to consent), confirmation of eligibility to take part, the consent process and randomisation, both groups will receive an initial assessment using the following scales: the Bristol Activities of Daily Living Scale (BADLS)
[29], Standardised Mini-mental State Exam (SMMSE)
[30,31], the Client Services Receipt Inventory (CSRI)
[32], The Model of Human Occupation Screening Tool (MOHOST)
[33] and the EuroQol EQ-5D
[34]. Unpaid carers of participants will be assessed over the same intervals using the Zarit Burden Inventory (ZBI)
[35], The Centre for Epidemiological Studies Depression Scale (CES-D10)
[36], the State Trait Anxiety Inventory (STAI-6)
[37], the Short Form Health Survey (SF-12v2)
[38] and the Carer Technology Acceptance Questionnaire (SUTAQ)
[39]. All of the outcome measures have established validity and high levels of inter- and intra-rater reliability. No pre-testing before randomisation is possible because of concerns by local authority hosts that this will delay the deployment of care and/or telecare to people who may have urgent needs for support.

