#### Cost-effectiveness

Costs will be calculated by attaching nationally applicable unit cost measures to health and social service use (collected at intervals stated above for each participant using a modified version of the CSRI), using national figures taken from the Personal Social Services Research Unit (PSSRU) annual compendium
[40] where available. The costs of ATT will be calculated anew for those services provided, and in this we will be guided by methods and experience gained in the WSD trial of telecare and telehealth
[25]. *Data on carer time and task inputs* will come from the CSRI, and will be valued using two approaches (replacement wage and opportunity cost) and then comparing the results in sensitivity analyses.

*Cost-effectiveness analyses* will be of two types to take into account the complication that the primary outcome (time to institutionalisation) is itself partly an indicator of resource use. Each type of analysis will then be conducted from each of two perspectives: for the ‘formal’ health and social care system (which is, for example, the perspective employed by the National Institute for Health and Care Excellence in England and Wales to appraise health technologies as a basis for producing clinical guidelines
[41]) and for society as a whole (which would then additionally include the value of carer time and any productivity losses from disrupted employment, either for the person with dementia or the carer).

The first type of cost-effectiveness analysis will measure costs only up to the point at which a study participant goes into a care home or hospital and not beyond (‘community costs’) and will then examine cost-effectiveness in achieving the primary outcome (days from randomisation to institutionalisation in the two year period). This analysis will show the incremental cost of community-based support for each additional institutional day avoided. The second type of analysis will measure costs for the whole 2-year period, including costs of care home and hospital stays (‘total costs’), and will then examine cost-effectiveness where the outcome is EQ-5D change, also over the 2-year period. We will also use the EQ-5D to generate Quality-Adjusted Life Year (QALY) measures by attaching societal weights
[42].

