### Secondary outcome measures

#### Burden in carers

We will measure both burden associated with care-giving and levels of psychological distress among the principal carers of participants at baseline, 12, 24, 52 and 104 weeks using the 22-item short version of the ZBI
[35].

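### The abstract ends assessments at institutionalisation, but the 2-year total-cost and EQ-5D analysis needs them to continue after a care-home move; the sections must be reconciled

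*Protocol article*

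**What the plan says.** The abstract (Method/design) gives a schedule with a stopping point: "Assessments will be undertaken in weeks 0 (baseline), 12, 24, 52 and 104 or until institutionalisation or withdrawal of the participant from the trial". The same paragraph ranks the outcomes: "Primary outcome measures are time in days from randomisation to institutionalisation and cost effectiveness".

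The Cost-effectiveness section, under Primary outcome measures, defines two analyses. The first counts community costs only up to entry to a care home or hospital. The second goes further: "The second type of analysis will measure costs for the whole 2-year period, including costs of care home and hospital stays", with effectiveness assessed "where the outcome is EQ-5D change, also over the 2-year period", and QALYs derived from the EQ-5D. Resource use for both is "collected at intervals stated above for each participant using a modified version of the CSRI".

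The Assessments section repeats the visit weeks with no stopping point: "Assessments will be undertaken by local investigators employed by the ATTILA team in weeks 0 (baseline), 12, 24, 52 and 104". It puts the EQ-5D and CSRI in that schedule, and the carer scales at the same intervals. The Burden in carers section likewise measures burden and distress "among the principal carers of participants at baseline, 12, 24, 52 and 104 weeks".

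The Analyses section, under Statistics, promises further follow-up where possible for participants who leave the study. It does not mention people who have moved to a care home.

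**The concern.** The abstract's rule and the second cost-effectiveness analysis cannot both be followed. The CSRI and EQ-5D are collected at the scheduled visits. If those visits end at admission, the second analysis has no EQ-5D and no CSRI for the time after the move, and that time lies inside its 2-year window.

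The gap is not random. A participant loses later data because he or she has reached the other primary outcome. Filling it from people still at home would assume that quality of life and service use after a move resemble those of similar people who did not move, and the trial would hold no post-move data to test that. The carer scales would be cut at the same point, although the Background names carer breakdown as a common reason for unplanned admission.

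**Working it through.** **The sections side by side**

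| Place | Visits | Stop at institutionalisation? |
|---|---|---|
| Abstract, Method/design | 0, 12, 24, 52, 104 | Yes |
| Assessments | 0, 12, 24, 52, 104 | None stated; continuation in a care home not stated |
| Burden in carers | 0, 12, 24, 52, 104 | None stated |
| Cost-effectiveness, first analysis | visits above | Costs stop at entry, which fits the abstract |
| Cost-effectiveness, second analysis | visits above | No: whole 2 years needed |
| Analyses | best effort after leaving the study | Institutionalised participants not named |

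**Inputs** (Sample size calculation): 500 participants; 50% institutionalised at 2 years in control and 35% with ATT; 10% attrition from death in the community; 55 days gained. Assumed here: 1:1 allocation, a 730-day window, no deaths.

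**The plan's own figures**
- Sample size: 50% v 35% at two-sided 5% and 90% power (neither stated in the article) needs 227 per arm, 454 in all. Allowing for 10% attrition, 454 × 1.1 = 499 and 454 / 0.9 = 504, or 505 rounded up. The stated 500 is reproduced.
- Days gained: if admissions are spread evenly over 730 days, each admitted participant spends 365 days on average in care within the window. Then (0.50 − 0.35) × 365 = 54.75, which is the stated 55 days.

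**Participants without a week-104 EQ-5D or CSRI if the stop is applied**
- Control: 250 × 0.50 = 125. ATT: 250 × 0.35 = 87.5.
- Total: 212.5 of 500 = 42.5%.
- With 225 per arm after 10% attrition: 112.5 and 78.75, total 191.25 of 450, again 42.5%.

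**Mean time after admission within 2 years, per randomised participant**
- Even timing: control 0.50 × 365 = 182.5 days (25% of 730); ATT 0.35 × 365 = 127.75 days (17.5%).
- Constant hazard λ = −ln(1 − p)/730, with mean time at home p/λ. Control: λ = 0.6931/730, so 526.6 days at home and 203.4 after admission (28%). ATT: λ = 0.4308/730, so 593.1 at home and 136.9 after admission (19%).
- Difference between arms: 54.75 days with even timing, 66.5 with constant hazard.

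**Earlier visits.** The Cost-effectiveness section also foresees analyses at 24 and 52 weeks. Under the constant hazard, 14.7% v 9.4% are already institutionalised at week 24, and 29.2% v 19.3% at week 52 (73 v 48 of 250).

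**If ATT has no effect.** Both arms would be near 50% at week 104. The gap would be balanced, but still large and tied to admission.

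**The case against.** The strongest defence is that the stopping clause stands only in the abstract. The Assessments, Cost-effectiveness and Burden in carers sections are all compatible with full follow-up, and the Analyses section asks for data as complete as possible. The clause may be loose wording. That is a fair reading, and it limits the finding to a conflict that must be resolved; it does not show that data will be lost. It does not remove the conflict, because no section says that visits continue after a move. One could also read an institutionalised participant as someone who has left the study, so that the best-effort follow-up applies. But the abstract names institutionalisation separately from withdrawal, and best effort is weaker than a scheduled assessment.

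Four stronger readings might be inferred. The documents do not support them.
- *That the saving from care-home days avoided goes unobserved.* The admission date is the primary outcome. Care-home days to day 730 follow by subtraction, given the date of any death, and can be priced with unit costs.
- *That adverse-event counts carry unequal exposure.* Nothing ties the recording of serious adverse events to these visits or ends it at admission.
- *That the EQ-5D and carer comparisons include only people still at home.* Repeated-measures regression is planned for continuous outcomes, so visits before admission still contribute. Informative dropout remains.
- *That the loss is certain to differ by arm.* That depends on ATT working.

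**Conclusion.** The point holds as an internal contradiction with consequences for one of the two cost-effectiveness analyses. If the abstract's rule is applied, post-move EQ-5D, hospital and other service use, and carer scales are missing for about 42.5% of participants by week 104. Mean post-admission time per participant is about 183 v 128 days with even timing, or 203 v 137 with a constant hazard.

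These sizes rest on the planning rates, 1:1 allocation and no deaths. The 50% rate is quoted for participants with a BADLS score above 15, which is not an entry criterion, so the actual share may differ. The missingness is informative in any case, and unequal by arm if ATT delays admission. Time to institutionalisation, the community-cost analysis and the costing of care-home bed-days stand.

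**What to change.** In the abstract, remove institutionalisation as an event that ends assessments. In the Assessments and Cost-effectiveness sections, state that after a care-home move the EQ-5D (by proxy if needed), a short CSRI covering care-home dates, hospital and other service use, and the carer scales continue at weeks 12, 24, 52 and 104, until death or refusal of data collection. In the Analyses section, say that institutionalised participants remain in scheduled follow-up and are not treated as having left the study.

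The cost is a change of wording and some extra follow-up contacts by researchers already employed for these visits. It should be settled while the trial is in progress, because an EQ-5D assessment missed after a move cannot be made later.

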**Discussion:**

In a time of financial austerity, CASSRs in England are increasingly turning to ATT in the belief that it will deliver good outcomes for less money. There is an absence of robust evidence for the cost-effectiveness and benefit of using assistive technology and telecare. The ATTILA trial meets a pressing need for robust, generalisable evidence to either justify continuing investment or reappraise the appropriate scale of ATT use.

**Trial registration:**

Current Controlled Trials
ISRCTN86537017

## Background

There are approximately 800,000 people with dementia in the UK
[1], many of whom will require accommodation in nursing or residential care homes when their illness has progressed to the point at which they can no longer live safely and independently in their own homes. It has been estimated that over the next 2 decades the number of people aged 85 and over will increase by two-thirds
[2]. Over half of all users of adult social care services are aged 65 and over
[3], and a steep rise in the numbers of people living with dementia is expected over the next few decades. The financial cost of caring for people with dementia is considerable
[1], as is the social and psychological cost to unpaid carers (generally a relative or friend, subsequently referred to as ‘carers’). Carer breakdown is a common reason for the unplanned admission of older people (many of whom will have dementia) into permanent nursing or residential care
[4].

Living Well with Dementia, the theme of the 2009 National Dementia Strategy for England
[5], involves helping people with dementia retain their independence while living in their own homes as well as to maintain their quality of their life. People living with dementia who move from their own homes into institutional care often experience a loss of independence and quality of life. In order to minimize this possibility, the National Health Service (NHS) and Councils with Adult Social Services Responsibilities (subsequently referred to as CASSRs) in England aim to support people with dementia to live safely in their own homes for as long as possible.

Assistive technology and telecare (ATT) offer relatively new means of delivering care and support to people with social care needs by helping to manage risks facing older people with dementia who wish to remain living independently at home. Sensors to detect falls, floods, or the presence of gas from an unlit appliance in someone’s home, for example; passive monitoring, for example, sensors placed within a home environment to detect movement; and alerting devices to relay information from the person’s home to a remote site such as a call centre are claimed to support the independence of people with social care needs, to reduce the burden on unpaid carers
[6-10] and to save CASSRs money. By addressing risks associated with independent living for people with dementia, ATT has claimed to help reduce the need for community care, prevent unnecessary hospital admissions, and delay or prevent admission into residential or nursing care.
[7,11-13] The evidence to support such claims is limited and based largely on qualitative evidence or uncontrolled quantitative studies
[14,15]. There is, therefore, an urgent need to provide evidence to inform decisions about whether to provide ATT in the homes of people with dementia. ATTILA is designed to answer questions about the efficacy and cost-effectiveness of ATT, with relevance for those who commission and provide care for people with dementia.

### Research evidence

The first use of electronic ATT in the UK, in the 1990s, was to provide support for people with dementia and their carers
[11,16-19]. Within a decade, interest in ATT has developed from a fringe interest for a handful of enthusiasts to a multi-million pound industry commanding government support, a Department of Health strategy
[20] and, increasingly, the use of ATT in CASSR settings as a mainstream service (see, for example
[19]). However, as interest in ATT has increased, the specific focus on its application for those living with dementia has diminished
[8]. The performance indicators that followed the Preventive Technology Grant (given to CASSRs in 2008 by the Department of Health
[20]) were intended to promote the widest possible use of telecare. The Department of Health did not, however, offer a clear indication of what this grant was supposed to ‘prevent’. Although Woolham
[7] has drawn attention to the cost-effectiveness of telecare for people with dementia by closely matching ATT with assessed need, and thereby preventing the need for more expensive forms of care, Poole
[21] has argued that CASSRs should see ATT as a long-term investment, deploying it at an early stage without expecting immediate savings. This has contributed to a situation in which CASSRs have implemented ATT across several different care groups without always referring to the needs of the specific groups, such as people with dementia. The current economic situation, as well as a significant reduction in government CASSR funding, has led to increasing numbers of CASSRs developing an interest in ATT. Some have developed local strategies to use it, whilst others already have well-developed ATT services that can be deployed alongside, or instead of, non-institutional forms of support, often known as ‘community care’ within the UK.

Despite growing ATT use, the evidence to support its use is limited. The Whole System Demonstrator study (WSD) was funded by the Department of Health in 2008 to investigate the impact and effectiveness of ATT in England

### Policy guidance

The Department of Health in England’s ‘Building Telecare’ strategy in 2005
[20] provided generic advice to CASSR. As part of this strategy, a Preventive Technology Grant, which CASSRs were required to spend on developing local ATT services, was made available. England’s 2009 National Dementia Strategy
[14] recommended a ‘watching brief’ for emerging evidence of the impact of telecare, stating:

*However, with respect to more recent innovations, this is not an area where the strategy is able at this time to make specific recommendations. Instead, central, regional and local teams should keep in touch with initiatives in the areas of housing and telecare and make appropriate commissioning decisions as data become available, for example from the Department’s large-scale field trials of telecare and assistive technology.* Department of Health (2009) p. 56

### Aim of the study

The aims of the ATTILA trial are to test the following hypotheses:

• That the application of ATT will significantly *extend the time* that people with dementia can continue to live independently and safely in their own homes.

• That ATT interventions are *cost-effective* in the management of risk and maintenance of independence in people with dementia living in their own homes.

• That provision of ATT interventions to people with dementia living at home will significantly *reduce the number of incidents* involving serious risks to safety and independent living, particularly those involving acute admissions to hospital,

• That ATT interventions will *reduce burden and stress* in family and other unpaid carers and *increase quality of life* for people with dementia.

### Objectives

These hypotheses will be tested by the following primary and secondary objectives:

#### Primary objectives

To establish whether ATT assessments and interventions *extend the time* that people with dementia can continue to live independently in their own homes and whether this is *cost-effective*.

#### Secondary objectives

(1) To establish whether these technologies can significantly *reduce the number of incidents* involving serious risks to safety and independent living, including acute admissions to hospital.

(2) *To reduce burden and stress* in family and other unpaid carers; and *increase quality of life* for people with dementia and their unpaid carers.

(3) To collect qualitative and quantitative data from people living with dementia, their paid and unpaid carers, and members of the NHS and CASSR teams about their *experience of using* these technologies.

## Methods

### Design

ATTILA is a pragmatic randomised controlled trial over 104 weeks. Blinding will not be undertaken as it is not feasible. It will be conducted in the homes of people living with dementia and who are eligible to receive a package of social care through CASSRs. The trial will compare outcomes in two groups of participants randomised to one of two study arms: either (1) receiving an ATT needs assessment, followed by the installation of ATT devices and response services which will be deployed by the CASSR, or (2) receiving a semi-structured ATT needs assessment, followed by the installation of an ATT package restricted to only smoke and carbon monoxide detectors and a pendant alarm if indicated, also arranged by CASSRs. The key outcomes will be *time to institutionalisation* and *cost-effectiveness* of the intervention.

The trial is not funded to source, assess the need for or deploy ATT. Our approach is therefore to work alongside CASSRs that have been charged by the Department of Health with responsibility for establishing and developing local ATT services.

The study has been approved by the NHS Health Research Authority National Research Ethics Committee (REC reference number 12/LO/186) and is registered with the ISRCTN (http://www.controlled-trials.com/ISRCTN86537017).

### Planned inclusion and exclusion criteria

#### Inclusion criteria

Participants will be people with dementia or evidence of cognitive difficulties significant enough to suggest the presence of dementia without having been formally diagnosed as having dementia, both with and without capacity. This will include those with young or later-onset dementia. Additionally, all participants must fulfil the following criteria:

• Meeting England’s eligibility criteria for access to social care services FACS (Fair Access to Care Services);

• Living in an ordinary community dwelling (including sheltered and very sheltered accommodation);

• Have a working telephone line in their home.

